### Design and setting

This is a non-blind, parallel-group (ratio 1:1), randomized controlled trial (superiority framework). The participants will be recruited from two colleges of Shiraz University of Medical Sciences in Iran: (1) School of Management and Medical Information (Health Information Management, Medical Informatics, and Health Services Management) and (2) School of Health.

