### Sample size

The sample size is calculated based on a similar previous study [41] where the mean (SD) of perceived stress in groups 1 and 2 were 7.43 (2.93) and 9.49 (3.06), respectively. This study was a research aimed to evaluate the efficacy of a stress management app for college students. We chose this randomized controlled trial study because it was very similar to our study in terms of the intervention, outcome, and participants. After that, the sample size is calculated using the NCSS software. The minimum sample size based on power = 80%, and *α* = 0.05 is estimated at 35 individuals in each group. In order to compensate for the loss to follow-up, we will increase the sample size to 50 individuals in each group.

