Both groups will have access to their specified apps for 3 months. All participants in the intervention and control groups will be requested to complete the questionnaires again after completion of the intervention.

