### Statistical analysis

The Kolmogorov-Smirnov test will be used to test the normal distribution of the data. The comparability of the intervention and control groups will be assessed at baseline. The quantitative variables will be described using mean and standard deviation if they follow a normal distribution and using median and range in case of non-normal distribution. The qualitative variables will be presented as percentages and confidence intervals. In order to compare the study groups regarding the mean scores of stress and sleep quality, the independent samples *t* test will be applied. In addition, the Mann-Whitney *U* and chi-square tests will be used to compare the two groups regarding non-parametric and categorical variables, respectively. In case of confounders, analysis of covariance or linear regression model will be used. Moreover, the paired samples *t* test will be utilized in order to compare the mean scores of stress and sleep quality in each group. Intention-to-treat analysis will be employed, as well. All analyses will be conducted using the SPSS 16 software, and *p* ≤ 0.05 will be considered statistically significant.

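### With an implied 30% loss to follow-up, the stated comparison of perceived stress ignores baseline PSS and the plan does not say whether intention-to-treat governs it

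*Protocol article*

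**What the plan says.** **Sample size (Protocol article).** The inputs come from a similar earlier trial, "where the mean (SD) of perceived stress in groups 1 and 2 were 7.43 (2.93) and 9.49 (3.06), respectively". With 80% power, the minimum at a significance level of "0.05 is estimated at 35 individuals in each group". The section then states: "In order to compensate for the loss to follow-up, we will increase the sample size to 50 individuals in each group". No loss rate is given.

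**Procedures and Data collection.** PSS is taken at baseline and once more when the 3-month intervention ends: "All participants in the intervention and control groups will be requested to complete the questionnaires again after completion of the intervention". There is no PSS measurement in between.

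**Statistical analysis.** The groups are compared on mean stress and sleep scores by the independent samples t test. ANCOVA or linear regression is held in reserve for the event that confounders are present. Near the end of the section comes one sentence: "Intention-to-treat analysis will be employed, as well". No analysis set is attached to the t test, and intention-to-treat is not designated as main or additional.

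**The concern.** Raising the number randomised protects power. It does nothing about bias if those who do not return the final questionnaire differ between arms. An independent t test on 3-month PSS can use only people who have a 3-month score, unless values are supplied for the rest. It also makes no use of baseline PSS, which is collected before the app links are sent and is the most obvious predictor of the final score.

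The Design and setting section says "This is a non-blind, parallel-group (ratio 1:1), randomized controlled trial (superiority framework". One arm gets a stress-management app and the other a calorie app. It is plausible that stressed students stay with the first and leave the second, or the reverse. In that case the scored groups no longer have equal baseline stress on average, and an unadjusted comparison carries that imbalance into the effect estimate.

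The t test on available scores, an adjusted analysis and an analysis that includes everyone randomised could give different answers. The text does not fix which of them is the trial's answer on its primary outcome. Making adjustment depend on whether confounders are found leaves that choice until the data have been seen.

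**Working it through.** **1. The plan's own figure.** Inputs from the Sample size section: means 7.43 and 9.49, SDs 2.93 and 3.06, power 80%, alpha 0.05. Allocation is 1:1 (Design and setting). Sidedness is not stated; two-sided is assumed, because a one-sided test would need only 27 per group.

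- Difference = 9.49 − 7.43 = 2.06.
- Pooled SD = √((2.93² + 3.06²)/2) = 2.996.
- Standardised difference = 2.06/2.996 = 0.688.
- Normal approximation: n = 2 × (2.996 × (1.960 + 0.842)/2.06)² = 33.2, so 34 per group.
- Noncentral t: 34 per group gives 79.8% power and 35 gives 80.9%.

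So 35 per group reproduces.

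**2. The implied loss.** 1 − 35/50 = 0.30, and 35/(1 − 0.30) = 50. The planned power therefore rests on about 35 scored participants per arm.

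**3. Where bias would come from.** Suppose dropout depends only on baseline PSS. Let r be the correlation of baseline with 3-month PSS, and D the between-arm difference in mean baseline, in SD, among those with a final score. Then:

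- bias of the unadjusted difference = r × D.

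If dropout has the same dependence on baseline in both arms, D averages zero and so does the bias. If the dependence differs, D is not zero. With r = 0.5, a bias of 0.06 SD needs D = 0.12 and a bias of 0.26 SD needs D = 0.52. Conditioning on baseline removes the term.

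**4. Size under assumed patterns.** The documents give neither r nor a dropout pattern. Assumed: 50 per arm, about 30% missing, r = 0.5, no true effect, 4,000 simulated trials per pattern, and dropout log-odds linear in baseline PSS per SD.

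| Dropout log-odds per SD of baseline | Bias of unadjusted t test (SD, absolute) | False positives |
|---|---|---|
| Same in both arms, 0.5 | 0.007 | 5.2% |
| Same in both arms, 1.0 | 0.001 | 4.4% |
| 1.0 in one arm, 0.5 in the other | 0.06 | 6.1% |
| One arm only, 0.5 | 0.07 | 6.2% |
| One arm only, 1.0 | 0.12 | 8.3% |
| Opposite directions, 0.5 | 0.13 | 9.4% |
| Opposite directions, 1.0 | 0.25 | 18.3% |

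A further run put the range for unequal patterns at 0.06 to 0.26 SD and 6 to 19%. Against the planned effect that is 0.06/0.688 = 9% to 0.26/0.688 = 38%.

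The baseline-adjusted model had bias of 0.01 SD or less and about 5% rejection. ANCOVA fitted only to those with a final score did equally well: 0.006 SD or less, 4.6 to 5.5%.

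**5. Power.** Adjustment shrinks the residual SD by √(1 − r²) = √0.75 = 0.866, so 0.688 becomes 0.688/0.866 = 0.794. With 35 per arm, 0.794 × √(35/2) = 3.32, and 3.32 − 1.96 = 1.36, which is about 91% power by the normal approximation. Simulation under random loss gave about 90%, against 81% for the t test.

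**6. What adjustment cannot reach.** If those lost in one arm differ from those retained, beyond what baseline explains, by 0.25, 0.5 or 1.0 SD, and that arm loses 30%, the comparison shifts by 0.30 times the gap: 0.075, 0.15 or 0.30 SD. That is 11%, 22% or 44% of 0.688. A delta-shift analysis shows how much of this the result would survive.

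**The case against.** A reader might infer that the headline result is to be a completer comparison, with intention-to-treat as a side analysis. The document does not support that. It attaches no analysis set to the t test, mentions no completer or per-protocol analysis, and asks all participants in both groups for the final questionnaire. The two closing words of the intention-to-treat sentence also end sentences about app features (Procedures) and app-use data (Data collection), where they are filler. The sentence can equally mean that the listed tests follow intention-to-treat. This stands, so the point is put conditionally.

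A reader might also infer that intention-to-treat could be done here only by carrying baseline scores forward. The plan never proposes that, and it names ANCOVA and regression itself.

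Missing-data methods are commonly left to a full protocol or analysis plan that is not shown, so their absence is no finding. That also stands. The point rests on what the article does state: an unadjusted comparison, adjustment only under a condition, and an intention-to-treat sentence that does not say what it governs.

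Finally, the largest figures come from opposite-direction dropout, which is an extreme assumption, and the bias vanishes when the pattern is the same in both arms. ANCOVA on scored participants removes it too. Under these dropout models the fault is therefore the lack of baseline adjustment; keeping participants who have only a baseline score is not essential to the cure. All of this stands. It narrows the point without removing it.

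**Conclusion.** The point holds in conditional form. The plan allows for an implied 30% loss, states an unadjusted t test for its primary outcome, and leaves open whether intention-to-treat governs it. If that test is run on available 3-month scores and dropout depends on baseline stress differently by arm, the assumed patterns give a bias of about 0.06 to 0.26 SD and a false-positive rate of 6 to 19%. Equal patterns give no bias.

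The figures rest on r = 0.5, 30% missing, and dropout driven by baseline PSS alone; none of these patterns comes from the documents. The sample size itself is sound. The change is worth making because the remedy is cheap and also raises power, from 81% to about 90% under the same r.

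**What to change.** State in the Statistical analysis section that the primary comparison of 3-month PSS is by randomised arm and adjusted for baseline PSS, whatever baseline comparisons show. Either form will do:

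- ANCOVA of 3-month PSS on baseline PSS, arm and college (college because randomisation used a separate list in each); or
- the equivalent linear mixed model with baseline and 3-month PSS as responses, a common baseline mean, and terms for time, arm-by-time and college. This keeps every randomised participant, including those with only a baseline score.

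Report the unadjusted t test as supportive. Add one delta-shift sensitivity analysis for missing 3-month scores. Say in one sentence what intention-to-treat means here and that it applies to the primary comparison.

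The cost is revised wording and a little more analysis. The number randomised stays at 50 per group, and baseline PSS is already collected. The adjusted analysis relies on data being missing at random given baseline and arm, which the delta-shift analysis probes. Trial status reports that recruitment has closed, so the choice should be recorded before outcomes are examined by arm.

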### Ethical aspects of the study

The present study was approved by the Ethics Committee of Shiraz University of Medical Sciences, Shiraz, Iran (IR.SUMS.REC.1398.664). Informed consent will be obtained from all participants, and confidentiality of the information will be assured.

## Discussion

This study aims to develop a web application and to determine its impact on stress management among college students. Development of the suggested web application and evaluation of its impact on the students will have the potential to develop useful media for managing stress, improving sleep quality, and providing information about the effectiveness of stress management strategies among college students who have been shown to experience high-stress levels. It has been hypothesized that the web application can reduce the stress level and improve the sleep quality among the target college students. It will also promote students’ healthy behaviors. Considering the fact that mental health services are limited in developing countries, many people cannot access fair resources, and only few applications developed in this field are evidence-based. Therefore, this theory-based web application is expected to be a promising tool to help students in Iran. To avoid the risk of contamination between the intervention and control groups, the web application will be available only to the intervention group by putting all intervention group participants in a white list and registering them in the web application. Then, web application registration will be disabled temporarily during the intervention, so that it cannot be used by anyone else. Overall, the study results will indicate an important step towards developing a technology platform for delivering a range of psychosocial strategies for managing stress and sleep problems.

### Trial status

This trial was registered in the Iranian Registry of Clinical Trials (IRCT20160427027647N2) on 14 May 2020. The recruitment began on 14 June 2020 and ended on 05 September 2020.

## Data Availability

Not applicable.

## Abbreviations

ACT: Acceptance and commitment therapy
SRT: Stress Reduction Theory
PSS: Perceived Stress Scale
PSQI: Pittsburgh Sleep Quality Index
